### Screening and group allocation

Participants will be screened over the telephone and only be invited to take part in the study if deemed eligible. Included participants will be assigned to one of two groups that will either receive an incentive during prospective memory tasks or not. Groups will be allocated using computer-generated random numbers, stratified by education, age, and sex.

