### Prospective memory task

To examine the neural substrates of event-based and time-based prospective memory, we will use a computerized task in the MR scanner [32], which will be presented with PsychoPy (v2021.1.2). The task will consist of four blocks: During the first and the third block, participants will perform a 1-back working memory task (as an ongoing-task), during which they will need to decide whether the current image is the same as the image presented just before (Fig. 2). Pseudorandom sequences of 238 Snodgrass & Vanderwart [33] pictures will be displayed on a screen for 2–3 s, followed by a 1–2 s inter-stimulus interval, used as a temporal jitter. During the second and the fourth block, a prospective memory task will be added to the ongoing task. One block will contain the event-based task and the other block the time-based task. The order will be counterbalanced across participants. In the event-based task, participants are asked to press a button whenever an animal appears on the screen (Fig. 2). Every answer that occurs within 5 s following the presentation of an animal will be considered as a prospective memory hit [32, 34]. In the time-based task, participants are asked to press a button whenever one minute has passed (Fig. 2). To monitor the time, they will be able to press another key to display a clock for 3 s in the upper left corner of the screen. Every correct response occurring ± 2.5 s around each target time will be counted as a prospective memory hit [32, 34]. Each prospective memory block will consist of 158 trials; out of these, 54 trials will be ongoing 1-back hits (i.e., trials in which the picture will be identical to the previous one), and 10 prospective memory cues (i.e., one every minute at 1:00, 2:00, 3:00… until 10:00) so that both tasks are similar. Each prospective memory block will last 10.5 min.

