### Statistical analysis

#### Behavioural: Do loss-related incentives enhance prospective memory?

Since we are primarily interested in whether incentives will enhance prospective memory, we will report accuracy and mean response times for the event-based task as well as accuracy and clock checking for the time-based task as primary outcomes.

First, we will test whether incentives will improve task accuracy. We will use two-way mixed-design ANOVA on correctly remembered trials, with the within-subject factor ‘task type’ (event-based or time-based) and the between-subject factor ‘group’ (incentive or control). Next, we will test whether response times in the event-based task will become quicker with an incentive. We will use one-way ANOVA on response times for correctly remembered trials, with the between-subject factor ‘group’ (incentive or control). For time-based prospective memory, we will test whether an incentive influences how often participants check the clock. Similar to our previous study [36], we will divide the 30 s before and after each target time into four intervals: T – 30 refers to the interval 30 to 15 s and T – 15 to the interval 15 to 0 s before target time. T + 15 or T + 30 then correspond to the intervals 0 to 15 s and 15 to 30 s after the target time. We will use a two-way ANOVA with the within-subject factor ‘time-interval’ and the between-subject factor ‘group’ (incentive or control). Finally, we will test whether monthly income, retirement status, personality traits, reward sensitivity, executive functions, or daily life prospective memory will predict performance. We will use linear regression with prospective memory accuracy as dependent variable and scores from the questionnaires as predictors. Age and gender will be included as covariates in all statistical analyses.

We will use R (Version 4.2.1) with Rstudio (Version 2022.02.3) for statistical analyses, with *p* < 0.05 considered statistically significant. We will correct for multiple comparisons using Tukey’s method. Whenever the assumptions of normality or homogeneity are not met, data will be transformed and/or non-parametric alternatives will be used. In case of missing data, we will use linear-mixed effects models rather than ANOVAs.

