### Are different brain regions involved in event-based vs. time-based prospective memory?

We will first analyse which brain regions are involved in event-based vs. time-based prospective memory. For the first-level analysis, we will fit one model for each prospective memory task. Each model will include three regressors, the first for ongoing trials during the ongoing task only block, the second for ongoing trials during the prospective memory block, and the third for prospective memory trials. We will build regressors using the onset of every correct answer. Task instructions will be modelled as regressors of no interest. We will define different contrasts corresponding to different prospective memory phases: 1) to obtain brain activity that is associated with maintenance of an intention, we will create contrasts between ongoing trials during the prospective memory block vs. ongoing only trials, 2) to obtain brain activity corresponding to the detection of a target, retrieval of an intention and its’ execution, we will create contrasts between prospective memory trials vs. ongoing trials during the prospective memory block. For time-monitoring, we will fit a model with the number of clock checks during the different time intervals previously described in the behavioural analysis. The onset will be defined as the moment in which the participant presses the key to check the clock. For time-monitoring, we will define contrasts between the different time intervals such as: T-15 vs. T-30, T-15 vs. T + 15, T-15 vs. T + 30, T-30 vs. T + 15, T-30 vs. T + 30, T + 15 vs. T + 30. Again, we will include six nuisance regressors for the six movement parameters as well as regressors of physiological data.

For second-level analyses, we will first use paired t-tests on first-level contrasts in the control group to test whether there would be differences in brain activity when comparing event-based to time-based prospective memory. Then, conjunction analysis will be performed to discern the neural substrates that are common in both task types. Then, we will calculate brain-behaviour correlations using beta estimates from significant regions correlated with task performance.

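### Education is a stratification factor and task order is counterbalanced, yet the fixed covariate list has only age and gender; the group tests stay unbiased but give up precision

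*Protocol article*

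**What the plan says.** Three parts of the protocol article bear on this.

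- **Screening and group allocation:** "Groups will be allocated using computer-generated random numbers, stratified by education, age, and sex". The Methods part of the abstract names the same three factors.
- **Prospective memory task:** one of the second and fourth blocks carries the event-based task and the other the time-based task. On which comes first: "The order will be counterbalanced across participants".
- **Statistical analysis, behavioural part:** accuracy is analysed with task type and group ("We will use two-way mixed-design ANOVA on correctly remembered trials"). Event-based response time is analysed with group alone ("We will use one-way ANOVA on response times for correctly remembered trials"). Clock checks are analysed with time interval and group. The covariates are then fixed: "Age and gender will be included as covariates in all statistical analyses".

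A separate regression looks at predictors of accuracy: "we will test whether monthly income, retirement status, personality traits, reward sensitivity, executive functions, or daily life prospective memory will predict performance". Education is not on that list.

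For the imaging comparison of the two tasks, "we will first use paired t-tests on first-level contrasts in the control group". The incentive and control groups are compared with two-sample t-tests. The imaging sections name no second-level covariates and do not mention order.

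**The concern.** Two of the three factors used to balance the groups are carried into the models. The third is dropped, and no reason is given. Stratifying on a factor that predicts the outcome makes the group difference less variable. A model that omits the factor cannot see this: it counts the factor's variance as noise and reports too large a standard error. The trial then bears the burden of stratifying without collecting the benefit.

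Task order is similar. Counterbalancing protects the comparison of tasks from a systematic shift between the second and fourth blocks. If that shift exists and order is not in the model, it adds to the spread of the within-person differences.

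At stake is precision in a study of 60 people whose power for the group effect is moderate. This is not detail that a condensed article merely leaves to a fuller plan, because the article itself fixes the covariate set for every analysis.

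**Working it through.** **Inputs from the protocol article.** N = 60, 30 per group; two task types; analysis alpha 0.05; f = 0.25; sample size figures of 54 participants, five measurements, alpha 0.01 and power 0.99.

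**Assumed, because the documents do not give them.** Within-person correlation 0.5; share of outcome variance explained by education after age and gender, R2, from 0 to 0.30; period effect from 0 to 0.8 SD of the within-person task difference.

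**1. The plan's own figure.** For a within-subject or interaction test, lambda = f² x N x m / (1 − rho) = 0.0625 x 54 x 5 / 0.5 = 33.75, with 4 and 52 x 4 = 208 degrees of freedom. At alpha 0.01 the power is 0.992, and 54 is the smallest even N that reaches 0.99. The figure reproduces. It contains no covariate, so this point does not change it. A between-group test under the same inputs would need 236, so 54 does not describe power for the group effect.

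**2. Power for the group effect on accuracy.** With two tasks, lambda = f² x N x 2 / (1 + rho) / (1 − R2). At R2 = 0 this is 0.0625 x 60 x 2 / 1.5 = 5.0. Error degrees of freedom are 60 − 4 = 56 with age and gender, and 55 with one further term for education.

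| R2 of education | lambda | Power, education included | SE factor 1/√(1 − R2) |
|---|---|---|---|
| 0 (reference, education not fitted) | 5.00 | 0.594 | 1.00 |
| 0.05 | 5.26 | 0.616 | 1.03 |
| 0.10 | 5.56 | 0.639 | 1.05 |
| 0.20 | 6.25 | 0.690 | 1.12 |
| 0.30 | 7.14 | 0.747 | 1.20 |

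**3. Check by simulation.** N = 60, 20,000 replicates, a two-level education factor balanced between groups, nominal 5% test, age and sex in both models.

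| R2 | Type I error, omitted | Type I error, included | Power at d = 0.65, omitted | Power at d = 0.65, included |
|---|---|---|---|---|
| 0 | 4.8% | 4.8% | 0.683 | 0.683 |
| 0.05 | 4.4% | 5.0% | 0.682 | 0.700 |
| 0.10 | 3.8% | 4.9% | 0.685 | 0.722 |
| 0.20 | 2.9% | 4.9% | 0.705 | 0.782 |
| 0.30 | 1.9% | 4.9% | 0.704 | 0.824 |

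At R2 = 0.20 the model without education reports a mean SE of 0.263, while the estimate's true SD is 0.235. The test is conservative. Because the omitting test also gains slightly from the balance, the gain from adjustment is a little smaller than step 2 alone suggests: 0.782 − 0.705 = 0.077 at R2 = 0.20, against 0.690 − 0.594 = 0.096.

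**4. Task order.** Let scores shift by π from the first to the second prospective memory block.

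- *Event minus time.* Each person's difference is the task effect plus or minus π, depending on order. In units of the SD of that difference, the variance becomes 1 + π² and the SE grows by √(1 + π²): 1.04, 1.12 and 1.28 for π = 0.3, 0.5 and 0.8. In simulation with order balanced within group, type I error for group x task fell to 4.2%, 2.7% and 1.2%, against about 5% with order in the model.
- *Mean of both tasks.* Everyone does one task first and one second, so everyone's mean contains π/2. The shift cancels, and type I error for the group main effect stayed at about 4.9% with or without order.
- *Single-task group comparisons (event-based response time, overall clock checks).* Here order separates people, half at +π/2 and half at −π/2. The SE factor is √(1 + π²/4), with π in SDs of the single score: √1.0225 = 1.01, √1.0625 = 1.03 and √1.16 = 1.08 for π = 0.3, 0.5 and 0.8.

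**The case against.** The strongest reply is that nothing here is invalid. Omitting a balanced factor leaves the group estimate unbiased and any error is on the safe side; counterbalancing already guards the task comparison against order bias. That stands. A reader might infer that the planned group comparison is biased or its significance level too liberal. The documents do not support this.

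A second reply is that the size is unknown. It depends on what education explains beyond age and gender, in a sample limited to ages 60 to 75 and screened for cognitive impairment. That also stands: the loss is nil at R2 = 0 and small at 0.05.

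A third reply concerns order. A reader might infer that leaving it out costs power for the main incentive effect on accuracy. It does not, since a pure period shift cancels from the average of the two tasks. The conservatism shown for group x task also assumes balance of order within each group, whereas the article says only that order is balanced across participants.

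Finally, a reader might infer that the paired imaging test in the control group loses a sizeable share of its 30 people. This goes too far. That test uses first-level contrasts. The retrieval contrast compares trial types within one block, so a shift common to both is subtracted out. The maintenance contrast compares a prospective memory block with ongoing-only trials, which removes much of the general drift if each task is paired with its preceding block. Only a period effect on the contrast itself remains. Main effects of age, sex and education cancel within person in the same test.

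None of this explains why education alone among the stratification factors is left out of a list that is fixed for all analyses.

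**Conclusion.** The point holds as one of precision. Education is used to form the groups and then omitted from the stated covariates, so the group tests are unbiased but conservative to the extent that education predicts the outcome. On the assumptions above, including it takes power for the group effect on accuracy from a reference of 0.594 to about 0.62, 0.64 and 0.69 at R2 of 0.05, 0.10 and 0.20. The benefit falls on between-group main effects; within-person terms such as group x task do not depend on the main effect of education.

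Omitting order can widen the error for task type, group x task and the single-task models, conditional on a period effect and on balance within group. It does not touch the group main effect on accuracy averaged over both tasks, and its imaging consequence cannot be sized from the documents. This is a cheap improvement worth making, not a threat to the study's conclusions.

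**What to change.** In the behavioural part of the statistical analysis, add education, coded in the form used for stratification, to age and gender in all group comparisons, and state that the same covariates apply to the two-sample second-level imaging tests. Add task order to the behavioural models, with order x task in the accuracy ANOVA to carry the period effect. Order may also be entered as a covariate in the paired event-versus-time imaging test, where the gain is limited to period effects on the contrast itself. It would help to state whether order is balanced within each group.

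The cost is a sentence or two. Education must be known at allocation and order is set by design, so no new data are needed. Order takes one degree of freedom and education with k levels takes k − 1, out of 60 − 4 = 56; with two levels, 54 remain. The number of education levels is not given. The change should be recorded before the data are analysed.

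### Four unranked primary outcomes give five incentive effects tested at 0.05, and the only behavioural multiplicity rule, Tukey's method, does not adjust across outcomes

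*Protocol article*

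**What the plan says.** All of this is in the protocol article, Statistical analysis, under the behavioural question on loss-related incentives.

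- **Primary outcomes.** The authors write "we will report accuracy and mean response times for the event-based task as well as accuracy and clock checking for the time-based task as primary". That is four measures for one question, whether an incentive helps prospective memory. None is ranked above the others.
- **Models.** There are three. Accuracy in both tasks goes into one mixed ANOVA with group and task type. Event-based response time goes into a one-way ANOVA with group. Clock checking goes into an ANOVA with group and four time intervals.
- **Level and adjustment.** The threshold is p < 0.05, followed by "We will correct for multiple comparisons using Tukey’s method". The family to which the correction applies is not defined, and no hierarchy or split of alpha is given.

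The Sample size calculation section plans with α = 0.01. The analysis section does not carry that level into the tests. The imaging analyses have thresholds of their own and are not part of this point.

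**The concern.** The three models contain five effects that could be reported as an incentive effect:

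1. accuracy: group main effect
2. accuracy: group × task type
3. response time: group
4. clock checking: group main effect
5. clock checking: group × interval

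Tukey's method controls the error over pairwise differences between means in one model. It has no mechanism for combining the accuracy, response-time and clock-checking models, so the five effects are tested with no joint control. Because no outcome is singled out and no success rule is given, a single significant result among them could be presented as evidence that incentives work. The 5% error rate would then not apply to the study's main behavioural conclusion.

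**Working it through.** **The plan's own figure.** The article gives no familywise error to reproduce. Its sample size does reproduce. The inputs are f = 0.25, 2 groups, 5 measurements, α = 0.01 and power 0.99. I assumed a correlation of 0.5 between measurements and no sphericity correction. The within-between interaction test, with λ = f²·N·m/(1 − ρ), then gives N = 54 with power 0.992. This shows only that the study was planned at a stricter level than the one used for testing.

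**What Tukey does to the group effect.** With two groups and 58 degrees of freedom (60 − 2), a two-sided p of 0.05 corresponds to a studentized range of t·√2, whose tail probability is again 0.05. One comparison stays one comparison. For the four clock intervals there are 4·3/2 = 6 pairs, and there Tukey does real work.

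**Familywise error under independence.** The formula is 1 − (1 − 0.05)^k.

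- Three group main effects: 1 − 0.95³ = 0.143
- All five incentive effects: 1 − 0.95⁵ = 0.226

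**Allowing for correlation.** The article gives no correlations between outcomes, so I took a common value r from 0 to 0.7 as an assumption. The planned ANOVAs were simulated with no incentive effect: 30 per group, normal data, 40,000 data sets per setting, a correlation of at least 0.5 among the clock intervals, and no covariates.

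| r | three group main effects | all five effects |
|---|---|---|
| 0 | 14.1% | 22.5% |
| 0.3 | 13.1% | 21.6% |
| 0.5 | 11.5% | 20.3% |
| 0.7 | 9.6% | 18.3% |

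The five-effect rate falls slowly because, with equal correlations, the two interactions are nearly independent of the main effects. As a check at r = 0.7: 1 − (1 − 0.096) × 0.95² = 0.184, close to the simulated 18.3%.

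**What a working rule would give.** Bonferroni over five effects uses 0.05/5 = 0.01 each, and 1 − 0.99⁵ = 0.049. That is the level used in the sample size calculation.

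**The case against.** **The size depends on a success rule that the article does not state.** This is the strongest objection. Each test has its own question: accuracy should improve, event-based responses should get faster, and clock checking may change in either direction. The Discussion treats enhancement mainly as accuracy. An interaction without benefit is not enhancement. Counting only false results in the beneficial direction (2.5% each), accuracy and response time give 1 − 0.975² = 4.9%, and three main effects give 1 − 0.975³ = 7.3%. This stands as a limit on the size. It does not remove the point: on that directional count a single test would give 2.5%, and the article does not say which result decides.

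**Tukey is not misplaced as such.** It has a proper use for the four intervals and the group-by-task cells. A reader might infer that leaving a two-level group factor unadjusted is itself an error. It is not, because one comparison needs no adjustment within its model. The gap is across models.

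**It could be left to an analysis plan.** An article that was silent on multiplicity could claim this. This one names its method, and the method does not cover its list of primary outcomes.

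**This is a mechanistic study of 60 healthy volunteers.** That bears on severity, and I have taken it into account.

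**Conclusion.** The point holds and should be fixed. The stated multiplicity rule does not control the error across the primary outcomes. If any one significant incentive effect counts as support, the familywise error is about 10 to 14% for the three group main effects and about 18 to 23% for all five, over assumed correlations of 0.7 down to 0. The any-one-counts rule and the correlations are both assumptions.

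Two stronger readings are tempting, but the article does not support them.

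- A reader might infer four separate tests at 0.05, and hence a false-positive chance of 19 to 23% as a plain fact. The two accuracy outcomes share one model, so there is no planned set of four tests. Figures such as 1 − 0.95⁴ = 18.5% and 22.6% hold only under independence and the any-one-counts rule.
- A reader might infer that the clause on failed assumptions, "data will be transformed and/or non-parametric alternatives will be used", inflates the error further, since accuracy is a count of hits out of 10. The article gives no expected accuracies, variances or effects from which to size this. A transformation keeps the interaction and the covariates, and rank-based factorial methods exist. I count this clause as no part of the error.

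**What to change.** Replace the multiplicity sentence with an explicit order of testing, before outcome data are compared by group.

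- **Preferred.** The group main effect on accuracy in the mixed ANOVA is the single primary test, at 0.05. Only if it is significant, test the remaining four incentive effects (group × task type, response time, clock checking by group, and group × interval) with Holm. The steps are 0.0125, 0.0167, 0.025 and 0.05.
- **Alternative.** Apply Holm across all five effects, with steps 0.01, 0.0125, 0.0167, 0.025 and 0.05. This suits the authors better if they expect an incentive to help only one task, because the averaged main effect could then miss it and stop the sequence.
- **In either case.** Keep Tukey for pairwise interval or cell comparisons within an ANOVA, and say so.

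The condition in the first option is needed. One test at 0.05 beside a separate Holm family at 0.05 would leave up to 1 − 0.95² = 9.75% under independence.

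The cost is analysis wording only, with no change to participants, procedures or sample size. The downside is a stricter threshold for the other outcomes and, under the first option, no confirmatory claim on them if the primary test fails. As an optional extra, a prespecified binomial mixed model for hits out of 10 would suit the accuracy data.
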